## Abstract

**Background:**

The prognosis for young people diagnosed with diabetes during childhood remains poor and this is mainly related to the long-term risk of developing vascular complications.

Microalbuminuria identifies subjects at risk for diabetic nephropathy (DN) and cardiovascular disease (CVD). It is often detected in adolescence but is rarely treated before the age of 18 years, as at the end of puberty albumin excretion may decline and in some subjects will return into the normal range. However, evidence indicates that subjects with both transient and persistent microalbuminuria have experienced renal damage during puberty and thus reno-protection to prevent long-term complications is warranted. In adults with diabetes and microalbuminuria, the use of angiotensin converting enzyme inhibitors (ACEI) and Statins is increasing, and in order to determine whether these agents are of value in the adolescent population a large randomized controlled clinical trial is needed.

**Methods/Design:**

The Adolescent type 1 Diabetes cardio-renal Intervention Trial (AdDIT) is a multi-center, randomized, double-blind, placebo-controlled trial of ACEI and Statin therapy in adolescents with type 1 diabetes. 500 high-risk adolescents, defined on the basis of their albumin excretion, are randomized to receive either ACEI (Quinapril) or Statins (Atorvastatin) or combination therapy or placebo for 3-4 years. There will also be a parallel open observational study, based on the follow-up of 400 low-risk non-randomized adolescents. The major endpoint of the study is the change in albumin excretion; secondary endpoints include markers of CVD, renal function, retinopathy, quality of life combined with assessment of compliance and potential health economic benefits.

**Discussion:**

AdDIT will provide important data on the potential renal and cardiovascular protective effects of ACEI and Statins in high-risk adolescents. Long-term follow-up of the randomized subjects will provide direct evidence of disease outcomes, in addition to the data on early surrogate measures of DN and CVD. Follow-up of non-randomized low-risk subjects will determine the potential impact of intervention on DN and CVD. AdDIT will help to determine whether, in addition to encouraging young people to achieve good glycaemic control, pharmacological cardio-renal protection should also be implemented.

**EudraCT Number:**

2007-001039-72

**Trial Registration Number:**

ISRCTN91419926

## Background

### Prognosis and complications of Type 1 Diabetes

The prognosis for childhood-onset type 1 diabetes (T1D) remains generally poor [1,2] and although life expectancy has increased by several years, reflecting increased longevity in the general population, the number of life years lost has remained unchanged over the last four decades and is about 17 years for a child diagnosed at the age of 10 years [3]. A recent study from Norway indicated that childhood-onset T1D is associated with a four-fold increase in the overall standardized mortality rate (SMR) [4], reflecting similar data from the USA [3]. By the age of 20 to 39 years the SMR for coronary heart disease in the British Diabetic Association Cohort of 23,000 patients diagnosed aged less than 30 years was increased ten-fold for men and forty-fold for women [2]. In the second decade after diagnosis diabetic nephropathy (DN) accounts for around 60% of deaths, whereas by the third decade cardiovascular disease (CVD) accounts for two thirds of all deaths [5]. However patients with nephropathy have approximately a forty-fold increased mortality from CVD [6]. The morbidity and mortality in childhood-onset diabetes is overwhelmingly associated with the development of long-term microvascular and macrovascular complications. Although complications are rarely seen during childhood, there is evidence that their pathogenesis begins soon after diagnosis and accelerates during puberty [7,8]. Thus, adolescence may be a critical period for lifetime risk of complications in childhood onset T1D.

### Seeds of future complications in adolescence

Glycated hemoglobin levels (HbA1c) during puberty are invariably higher than levels recommended for prevention of complications. In the Diabetes UK National Audit the mean HbA1c in those aged under 16 years was 8.9% and only 72% had an HbA1c less than 9.5% [9]. In the Diabetes Control and Complications Trial (DCCT), although adolescents showed the same benefits from intensified therapy as adults, HbA1c levels were generally 1% higher and excess weight gain and hypoglycaemia were more frequent in the adolescents [10,11].

It is during puberty that the first signs of complications become evident and microalbuminuria (MA), an early risk marker for DN and CVD [12,13] may be found in 12-16% of adolescents [13-17]. This has been associated with renal pathology indicative of early nephropathy [18]. The relationship between puberty and MA is only partly explained by poor glycaemic control and there is evidence that puberty itself may be an independent risk factor [13,19]. The development of MA is associated with hyperlipidemia [20,21], elevation of arterial blood pressure [22], decline in renal function [23] and retinal changes [24]. It has been suggested that MA represents the first evidence of a generalized endotheliopathy [25]. Flow mediated dilation (FMD), an established marker of endothelial function, may be abnormal in adolescents with T1D [26] and carotid artery intima-media thickness (cIMT), a marker of early atherosclerosis and a strong predictor of future vascular events [27], has been found to be increased in adolescents with T1D [26,28-32]. Markers of sub-clinical atherosclerosis, including cIMT, have been linked to the development of MA in the general adult population [33]. Markers of endothelial dysfunction and arterial stiffness have also been associated with MA in diabetic populations [34,35]. Thus rapid growth and poor glycaemic control during adolescence both contribute to the future complications risk associated with MA.

### Intervention in adolescents to prevent future complications

It has been argued that early intervention in adolescents with MA is unnecessary as it may revert to normal at the end of puberty in 50% of patients [36-40] and only around 15% will progress to clinical proteinuria. Recent data from the Oxford Regional Prospective Study (ORPS), which has been following an incident cohort of around 500 children since 1986 [13,41], indicate that MA is transient in 39% and with continued follow up, 48% of subjects have persistent MA and 13% have intermittent MA. 4% of the ORPS cohort has developed clinical proteinuria and this is related to both persistent (hazard ratio (HR): 27.7) and intermittent MA (HR 8.8) [41]. The cumulative probability of developing clinical proteinuria was 13.9% after 18 years diabetes duration in this population, diagnosed at 9.5 years [41] compared with a rate of 14.6% in the only adult incident cohort after a similar duration of diabetes [42]. Risk for MA can be identified by greater rates of albumin excretion, although still within the normal range, as early as one year from diagnosis [43] and we have recently shown that albumin excretion in the highest tertile after adjustment for age, gender, duration of disease and age of diagnosis, at age 11-15 years, predicts 85% of subjects who go on to develop MA and all of the subjects who develop clinical proteinuria [44]. Therefore early abnormalities in albumin excretion during adolescence are predictive of complications risk and early intervention in high-risk adolescents could lead to long-term improvements in prognosis.

### Previous interventions with ACEI and Statins

T1D adults with both intermittent and persistent MA are increasingly being treated with angiotensin converting enzyme inhibitors (ACEI) or angiotensin receptor blockers (ARB), as these drugs have been shown to reduce risk of progression of MA to clinical proteinuria and may also be effective in reducing mortality from CVD [45]. Screening for MA is routinely recommended during adolescence [46,47], yet recommendations for treatment are not consistent. Four small studies have confirmed the likely efficacy of ACEI in adolescents with MA, but there have been no formal randomized controlled trials (RCTs) [48-51]. In a review of 12 adult trials of ACEI, reductions in albumin excretion rates of 50.5% (95% CI: 29.2-65.5) [52] were similar to those observed in the adolescent studies: 41% [48] and 55-60% [49]. In the study reported by Rudberg [53], reductions in albumin excretion were associated with improvement in renal biopsy changes in young patients with T1D. A beneficial effect of ACEIs treatment, has also been demonstrated for diabetic retinopathy [54]. The EURODIAB Controlled Trial of Lisinopril in T1D showed a significant effect of lisinopril in reducing by around 50% the progression of retinopathy in normotensive and normo- or microalbuminuric patients [54]. In the recent Renin-Angiotensin System Study, treatment with either enalapril or losartan reduced progression of retinopathy by 65-70% [55].

Hyperlipidemia is commonly reported in adolescents with T1D [20,21] but there have been no studies of statin therapy in this population. Treatment with HMG-CoA reductase inhibitors (Statins) is becoming increasingly common in adults as they reduce major vascular event rates by about one third in T1D subjects aged > 40 years [56]. The National Institute for Health and Clinical Excellence guidelines recommend statin treatment for T1D adults with MA or two or more features of the metabolic syndrome and the recent Joint British Societies' Guidelines [57] recommend statin treatment in adults with persistent MA. Management depends on extrapolating from the results of trials conducted in adults with diabetes [58] and short-term trials of up to two years duration conducted in children with familial hypercholesterolemia (FH) that show treatment to be efficacious and safe [59,60]. Longer-term trials in children and adolescents with T1D are therefore urgently needed to address clinical uncertainty [61].

Clinical trials may need to use surrogate endpoints and non-invasive vascular assessment techniques have demonstrated abnormalities in T1D in early childhood [26,28-32,62]. In particular, cIMT has been shown to be significantly greater in children with T1D than in age-matched controls [26] and not dissimilar to that observed in heterozygote subjects with FH [63]. Other measures of CVD risk and endothelial dysfunction, such as FMD, may precede changes in cIMT within the first decade of T1D in children [26] and other measures such as endothelial pulse amplitude tonometry (EndoPAT) may also distinguish T1D from healthy subjects [64-66]. Arterial stiffness as assessed by pulse wave velocity (PWV) may be an additional marker of CVD, which has been shown to be abnormal in T1D patients as young as 10 years [67]. Statin treatment would be expected to slow the progression or result in regression of cIMT, and a two-year RCT of pravastatin in 214 children with heterozygous FH found active treatment to result in a significant difference in the mean change in cIMT between the two groups [68]. In addition to reducing the risk of CVD, statin therapy may also reduce the risk of nephropathy. Low density lipoprotein (LDL) cholesterol, and small dense LDL in particular, produce proliferative and biosynthetic responses in glomerular cells that occur in the early stages of DN [69]. Mesangial cells can take up both native and modified LDL and respond in vitro by proliferation, production of chemo-attractants for monocytes and macrophages, and alterations to matrix turnover leading to net matrix expansion [70]. Furthermore, diabetes induced mesangial expansion has been shown in animal models to be reduced in a dose dependent manner by statins [71]. Statin treatment is associated with a significant reduction in mean serum creatinine concentration [72] and a recent trial of subjects with diabetes reported a reduction of 11% in patients randomized to atorvastatin for three years whilst patients randomized to standard care showed a 5% increase in creatinine [73]. These findings suggest that statin therapy in T1D may reduce the risk of both DN and CVD. Dyslipidemia has also been implicated in the pathogenesis of retinopathy and consequently statin treatment may be beneficial in limiting this complication [74,75]. Combination therapy with a statin and an ACEI for patients at high risk of development of MA may therefore represent the most effective strategy for reducing future morbidity and mortality from DN and CVD in patients with childhood-onset T1D. Thus both ACEI and Statin therapy could provide cardio-renal protection in high-risk subjects during adolescence and we plan to explore this hypothesis through a randomized controlled trial.

## Aim Of The Study

To carry out a multi-center, randomized, double-blind, placebo-controlled trial of ACEI and Statin therapy in adolescents with T1D. 500 adolescents at high risk for DN and CVD will be randomized to receive either ACEI or Statins or combination therapy or placebo for three to four years (**Study 1**). There will also be a parallel open observational study, based on the follow-up of 400 low-risk non-randomized adolescents (**Study 2**).

## 1. Randomised Controlled Clinical Trial (Study 1)

### Study Objectives

#### Primary

To determine whether intervention with ACEI, Statins, or combination therapy when compared with placebo, in a 2 × 2 factorial design over three to four years, will: 1) reduce albumin excretion as assessed by six monthly measurement of albumin/creatinine ratio (ACR) in 3 early morning urines; 2) reduce the incidence of MA (ACR >3.5 mg/mmol (males) or >4 mg/mmol (females) in 2 out of 3 urines) at the end of the study period; 3) reduce the incidence of MA during the six month run-out period following the completion of intervention phase.

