### Study endpoints

The primary endpoint is defined as the area under the curve over time of log ACR per year, with standardization for gender, age and duration of diabetes.

The secondary endpoints are: 1) changes in cIMT, FMD, EndoPAT and PWV between baseline and the end of intervention period; 2) changes in arterial BP, lipids and other lipoproteins, CVD risk markers (hsCRP and ADMA), assessed every 6 months during the intervention period; 3) changes in measures of GFR (plasma SDMA, creatinine and cystatin C) assessed every 6 months during the intervention period; 4) changes in retinopathy scores and retinal microvascular structure (arteriolar or venular dilation, vascular fractal dimension, branching and tortuosity), assessed annually; 5) changes in quality of life and health economics.

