##### • Sample size determination and power calculations

*Number of Subjects required*

The primary power calculation estimates that 400 subjects will need to be analyzed and we aim to recruit 500 to allow for dropouts and non-compliance.

*Power calculations based on the primary endpoint*

A 30% reduction in ACR is considered a worthwhile and plausible effect size to detect in this population and detection of a 25% reduction would be an advantage. With the 2 × 2 factorial design we plan for follow-up of 100 patients in each of the four arms: Placebo (P), ACEI (A), Statin (S), combination of ACEI and Statin (C). This sample size is informed by the ORPS cohort study (477 participants in the correct age range of recruitment with a mean of 3.5 observations over time) [13]. Within the tertile with the highest ACR standardized for gender, age and duration (defined as standardized ACR > 1.2), the standard deviation (SD) of standardized log to base 10 of ACR was 0.38 (mean 0.28) based on analyzing the final value alone, whereas the SD of the average standardized log ACR repeated over time, defined as area under curve per year, was 0.28 offering a reduction in detectable effect size from 30% to 25%. The primary endpoint is therefore defined as area under curve of log standardized ACR, with standardization for gender, age and duration of disease. The chosen sample size and endpoint provide 93% power to detect a 25% reduction in ACR attributable to the factorial main effect of ACEI (A and A+S arms [n = 200 total] versus P and S arms [n = 200 total]), and of Statin (S and S+A arms [n = 200 total] versus P and P+A [n = 200 total]). Additionally there is 82% power to detect a 30% reduction in ACR, in the following single-arm comparisons: A [n = 100] versus P [n = 100]; S [n = 100] versus P [n = 100]; and S+A [n = 100] versus P [n = 100].

*Power calculations for secondary endpoints*

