For secondary outcomes, a 1% level of significance will be applied. For continuous outcomes, the sample size allows detection of small to moderate effect sizes; there will be 82% power in single arm comparisons to detect effect sizes of 0.5 SD between arms, and 93% power for factorial main effects of size 0.4 SD. For the secondary outcome cIMT, a pooled estimate across two studies of the SD of change from baseline is 0.044 [68]. There is 93% power to detect a 0.018 mm difference for ACEI and Statin factorial main effects, and 82% power to detect a 0.022 mm difference for single-arm comparisons.

For the secondary outcome FMD, an estimate across recent studies of the SD of change from baseline is 2.5. 180 subjects will give 80% power to detect a 1.5% difference in FMD between baseline and final assessment at a 5% level of significance.

For the secondary outcome PWV, an estimate across recent studies of the SD of change from baseline is 1.5. 200 subjects will give 80% power to detect a 0.85 m/sec difference in PWV between baseline and final assessment at a 5% level of significance.

For the secondary outcomes retinopathy and subclinical changes in the retinal microvasculature, the sample size will give greater than 90% power to detect a 25% difference in retinopathy prevalence and to detect a minimum of 3% change in retinal vascular parameters.

For binary outcomes, the sample size allows detection of moderate to large difference in proportion effect sizes, when the proportion is the mid-range of 0.2 to 0.8; so that there is 93% power to detect factorial main effects of a 50% relative reduction for proportions 0.4 versus 0.2, and the corresponding relative reduction detectable for the single-arm comparisons is 58%. For the secondary outcome of MA over the two measurements at age 18, the detectable reduction for factorial main effects is prohibitively large, 75%, due to a necessarily low prevalence in the treated arm, and therefore the more sensitive continuous ACR outcome will be the primary indicator of MA.

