##### Run-out assessments

At the end of the intervention period and following the final study assessment, all study drugs will be withdrawn and subjects will be followed for a 6-month run-out period. At the end of this period subjects will be asked to provide a final blood sample and three early morning urines for assessment of ACR and MA status and measurement of lipids, lipoproteins, CVD risk markers, SDMA, creatinine and cystatin C. These data will be used to inform physicians as to the need for re-starting IMP according to local prescribing guidelines in subjects aged 15-19 years.

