### Statistical analysis

Continuous measures will be compared between groups using analysis of covariance, whereas binary outcomes will be compared using logistic regression. These models will involve adjustment for the randomization stratifiers, and for pre-randomization baseline outcomes to improve precision. The primary endpoint was correlated with baseline standardized ACR in the ORPS cohort (r = 0.3) indicating potential improvement in precision of estimated treatment effects. An initial test will be undertaken for exclusion of the factorial interaction of ACEI with Statin, with subsequent estimation of the factorial main effects of ACEI and Statin and single-arm comparisons. Subgroup analyses, for gender and for baseline standardized ACR (using a median split), will be undertaken by adding an interaction between the subgroup variable and factorial main effects followed by estimation within subgroups. Sensitivity analyses, such as for compliance and for raised HbA1c, will involve analysis using the same methods but applied omitting the relevant subjects or the relevant observations within subjects. For the HbA1c sensitivity analysis exclusions will be defined as those observations following the initial occurrence of a change in HbA1c from baseline in excess of 1%. An analysis restricted to the initial two measurements (first year) where short-term compliance is considered greater, will be performed and contrasted with the later period using within-patient analysis. Missing data will be primarily handled by excluding missing observations from analysis and secondly by multiple imputations [91] considering a contrast of both optimistic and pessimistic scenarios for treatment effects. Analyses will be on the primary basis of intention to treat, with as treated and per protocol as secondary. All tests will be two-tailed, and 5% and 1% significance levels will be used for primary and secondary outcomes respectively.

Formal interim analyses have not been incorporated into the design and analysis of the trial because the 3 to 4 year period of follow-up per subject is long relative to the recruitment period, and an interim analysis would detect early improvements without informing maintenance of any effect. The independent DMEC will determine how regularly to review efficacy and safety regularly, based on progressively longer mean treatment durations.

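### The run-out, the only planned drug-free randomised comparison of albuminuria, has its objective fixed only as incidence of MA, and the continuous ACR collected there is not named as an endpoint

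*Protocol article*

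**What the plan says.** All references are to the Protocol article.

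- **Study Objectives, Primary.** The third objective is to "reduce the incidence of MA during the six month run-out period following the completion of intervention phase". The second objective defines MA as "ACR >3.5 mg/mmol (males) or >4 mg/mmol (females) in 2 out of 3 urines", which is binary.
- **Run-out assessments.** All study drugs are withdrawn after the final assessment. At the end of six months each subject gives "three early morning urines for assessment of ACR and MA status". The continuous value is therefore collected, at one visit.
- **Study endpoints.** "The primary endpoint is defined as the area under the curve over time of log ACR per year". No run-out endpoint is listed. The six-monthly secondary endpoints (blood pressure, lipids, CVD markers, GFR) are limited to the intervention period.
- **Power calculations for secondary endpoints.** For MA at age 18, "the detectable reduction for factorial main effects is prohibitively large, 75" (per cent). The sentence goes on to make continuous ACR the main indicator of MA.
- **Statistical analysis.** Continuous measures go to ANCOVA and binary outcomes to logistic regression, both adjusted for the randomisation stratifiers and baseline outcomes. Tests are two-sided, at 5% for primary and 1% for secondary outcomes.

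**The concern.** The primary endpoint summarises ACR over follow-up. A lower value in a treated group could mean that the kidney has been protected, or only that albumin excretion is suppressed while tablets are taken. The run-out is where the randomised groups can be compared on albuminuria with both drugs stopped. Its objective is stated only on the scale that the power section sets aside as too insensitive, and the more sensitive measurement from the same urines has no endpoint.

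If the AUC result were positive and the run-out MA result inconclusive, the trial could not say whether three to four years of treatment had a lasting effect. That matters because the article's rationale is reno-protection during puberty.

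**Working it through.** **1. The protocol's 75% figure.** No control prevalence is given, so the figure cannot be reproduced directly. Taking 93% power, two-sided 1% and 200 v 200 from the surrounding text, and solving for the control prevalence with a pooled two-proportion test, gives about 16.2% v 4.0% (17.3% v 4.3% with continuity correction, 15.0% v 3.7% by arcsine). The figure is therefore plausible. On a normal log10 ACR scale, 16.2% v 4.0% is a shift of 1.746 − 0.988 = 0.758 SD. With SD 0.38 that is 0.288 log10 units, a fall in ACR of 1 − 10^(−0.288), or about 48%. The protocol calls 30% worthwhile and says that detecting 25% would be an advantage.

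**2. Inputs for the run-out comparison.**

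| Input | Value | Source |
|---|---|---|
| SD of log10 ACR, one time point | 0.38 | Sample size section: "was 0.38 (mean 0.28) based on analyzing the final value alone" |
| n per side, factorial main effect | 200 | Sample size section |
| Effect | 25% lower ACR: −log10(0.75) = 0.125 | Sample size section; persistence off drug is assumed |
| Alpha, two-sided | 5% or 1% | Statistical analysis |
| Control MA prevalence at run-out | 10-20% | Assumed; the Background gives 12-16% for adolescents generally, not for the high-risk tertile |

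The smaller SD ("defined as area under curve per year, was 0.28") belongs to repeated values and does not apply to one run-out visit.

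**3. Continuous log ACR.** SE = 0.38 × √(2/200) = 0.038. Ratio = 0.1249/0.038 = 3.29. Power = Φ(3.29 − 1.96) = 0.908 at 5%, and Φ(3.29 − 2.576) = 0.762 at 1%.

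**4. The same shift read as MA.** For control prevalence p0, the treated prevalence is p1 = 1 − Φ(z(1 − p0) + 0.1249/0.38). Power comes from the pooled two-proportion test.

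Example, p0 = 16%: z = 0.994 + 0.329 = 1.323, so p1 = 9.3%. The difference is 0.0671, the null SE 0.0332 and the alternative SE 0.0331. Power at 5% = Φ((0.0671 − 1.96 × 0.0332)/0.0331) = 0.52.

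| Control MA | Treated MA | Power, 5% | Power, 1% | Information kept |
|---|---|---|---|---|
| 10% | 5.4% | 41% | 20% | 34% |
| 16% | 9.3% | 52% | 29% | 44% |
| 20% | 12.1% | 58% | 34% | 49% |
| Continuous log ACR | – | 91% | 76% | 100% |

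Information kept is φ(z)²/[p0(1 − p0)], the efficiency of the binary reading relative to the continuous one.

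**5. Larger and smaller effects.** For a 30% lower ACR (0.155 log10), continuous power is 98% at 5% and 93% at 1%. MA has 55-75% and 31-52% over the same prevalences. If only a 12.5% reduction remained, −log10(0.875) = 0.058 and the ratio is 1.53. Continuous power at 5% is then Φ(1.53 − 1.96) = 33%. The step 4 formula gives MA 14-18% (p1 = 7.6% for p0 = 10%, 16.0% for p0 = 20%).

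**The case against.** **No run-out test is specified.** The article states an objective and collects the urines. It gives generic models and defers detail to a statistical analysis plan that is not shown. A reader might infer that the run-out will be tested only as yes/no; the text does not say so, and that plan may use the continuous value. What stands is that the objective is worded on one scale only and the endpoint list has no counterpart on the other.

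**The protocol already turns to continuous ACR.** It does, but in a sentence about MA at age 18 that names no run-out analysis. The AUC has no stated window either. If it were read to include the run-out, it would average on-drug and off-drug values and could not separate them.

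**This is not the only objective beyond treatment.** That is correct. Long-term DN and CVD incidence is a secondary objective, and a re-assessment including albumin excretion is planned five years after the study. That re-assessment depends on further funding, and the article allows drugs to be restarted after the run-out. The narrower statement, the only planned drug-free randomised comparison of albuminuria, holds.

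**Most of the power is not lost.** At 5% the binary outcome keeps 41/91 = 45% to 58/91 = 64% of the power over 10-20% prevalence. A reader might infer from the 1% figures that most of it goes, but that depends on an alpha and a prevalence the article leaves open.

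**The maintenance remark.** The Statistical analysis section says that "an interim analysis would detect early improvements without informing maintenance of any effect". This explains why there are no interim analyses. It should not be read as a statement about persistence after withdrawal.

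**Conclusion.** The point holds in limited form. The run-out objective is fixed only as MA incidence, an outcome type the protocol itself regards as too insensitive when it considers MA at age 18, and the run-out ACR is collected without being named as an endpoint. For a 25% lower ACR that persists off drug, the choice is between about 91% and 41-58% power at 5%, or 76% and 20-34% at 1%. Over 10-20% prevalence, dichotomising discards more than half of the information.

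The figures assume normal log10 ACR, the single-value SD carried to the run-out, 400 subjects analysed, MA as one threshold rather than two of three urines, no covariate adjustment, and the full 25% effect surviving withdrawal. The last is a favourable case. The continuous measure was stronger at every prevalence tried (5-30%), so the direction does not depend on the assumed prevalence. The applicable alpha is itself unclear: the objective is listed as primary, while the power section treats MA as secondary. Nothing is irretrievably lost, because the measurements are taken.

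**What to change.** Name the mean log standardized ACR of the three run-out urines as the run-out endpoint. Compare it by the factorial main effects of ACEI and statin, in the ANCOVA already planned, adjusted for baseline ACR and the minimization factors. State its significance level: a secondary outcome at 1% unless declared otherwise. Keep run-out MA as a supporting outcome.

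The cost is one more endpoint and one more test, on urines already collected. No visit or sample is added.
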